## Abstract

**Background:**

Major depressive episode (MDE) is worldwide one of the most prevalent and disabling mental health conditions. In cases of persistent non-response to treatment, electroconvulsive therapy (ECT) is a safe and effective treatment strategy with high response rates. Unfortunately, longitudinal data show low sustained response rates with 6-month relapse rates as high as 50% using existing relapse prevention strategies. Cognitive side effects of ECT, even though transient, might trigger mechanisms that increase relapse in patients who initially responded to ECT. Among these side effects, reduced cognitive control is an important neurobiological driven vulnerability factor for depression. As such, cognitive control training (CCT) holds promise as a non-pharmacological strategy to improve long-term effects of ECT (i.e., increase remission, and reduce depression relapse).

**Method/design:**

Eighty-eight patients aged between 18 and 70 years with MDE who start CCT will be included in this randomized controlled trial (RCT). Following (partial) response to ECT treatment (at least a 25% reduction of clinical symptoms), patients will be randomly assigned to a computer based CCT or active placebo control. A first aim of this RCT is to assess the effects of CCT compared to an active placebo condition on depression symptomatology, cognitive complaints, and quality of life. Secondly, we will monitor patients every 2 weeks for a period of 6 months following CCT/active placebo, allowing the detection of potential relapse of depression. Thirdly, we will assess patient evaluation of the addition of cognitive remediation to ECT using qualitative interview methods (satisfaction, acceptability and appropriateness). Finally, in order to further advance our understanding of the mechanisms underlying effects of CCT, exploratory analyses will be conducted using video footage collected during the CCT/active control phase of the study.

**Discussion:**

Cognitive remediation will be performed following response to ECT, and an extensive follow-up period will be employed. Positive findings would not only benefit patients by decreasing relapse, but also by increasing acceptability of ECT, reducing the burden of cognitive side-effects.

**Trial registration:**

The study is registered with ClinicalTrials.gov. Study ID: NCT04383509

Trial registration date: 12.05.2020.

## Background

Virtually all national and international guidelines consider electroconvulsive therapy (ECT) a valuable, effective, safe and tolerable therapeutic option in cases of treatment resistant major depressive episode (MDE) and for severe and life-threatening depressive conditions (i.e., psychotic depression, high suicide risk, life threatening malnourishment) [1, 2]. During the ECT procedure, performed under general anesthesia and a muscle relaxant to minimize side effects, epileptic activity is induced/generated by a controlled passage of electric current through the brain. Even though the exact neurobiological mechanism of action remains largely unclear, antidepressant effects are attributed to changes in neurotransmitter levels, improved neuroplasticity, increased functional connectivity, and an increase in plasmatic brain-derived neurotrophic factor (BDNF). The therapeutic efficacy of ECT for MDE is characterized by a fast onset of action and high initial response rates. Meta-analyses support superiority over pharmacotherapy [3] and response rates of 74,2% for MDE in unipolar patients and 77,1% for MDE in bipolar patients are reported [4]. The pooled remission rates, even in cases of treatment resistance, are 52,3% for unipolar and bipolar patients [4].

Unfortunately, longitudinal data show low sustained response rates with relapse rates as high as 84% within the first 6 months after ECT [5]. Relapse prevention strategies are therefore key to maintain remission after successful ECT and identifying new therapeutic options are necessary. Several strategies have been put forward to prevent relapse after ECT. These include the continuation of pharmacotherapy and especially, combining an antidepressant (nortriptyline or venlafaxine) and lithium. In a 2001 study, Sackeim and colleagues reported relapse rates of 39% for the combination of lithium and nortriptyline compared to 60% for nortriptyline monotherapy over a six-month period [5]. The latter benefits have been confirmed in more recent RCTs [6, 7], and a meta-analysis found 6-months relapse rates in modern post-DSM-III studies of 37.7% for patients treated with pharmacotherapy [8]. However, there is also growing evidence on the utility of more recently developed antidepressants such as venlafaxine (225 mg/day) as they have a more favorable side-effect profile [6]. Continuation ECT (c-ECT), where patients receive continued ECT at a reduced schedule after a successful index ECT course, is another valuable relapse prevention strategy. Relapse rates, 37.2% over a 6-month period, are comparable to continuation pharmacotherapy [8]. Kellner et al. (2006) reported even more favorable outcomes by combining continuation pharmacotherapy (venlafaxine + lithium) with ECT tapering and c-ECT as needed in a geriatric population [6].

Yet, given that current 6-month relapse rates remain high at 37,7% [8] despite the use of existing relapse prevention strategies, there is an urgent need for novel interventions. Hereby, interventions, based on the remediation of cognitive deficits that occur during and following ECT treatment, may offer an interesting opportunity. Cognitive impairment is an important symptom cluster in affective disorders and may continue to affect functional outcomes in a negative matter even after achieving remission of mood symptoms [9]. Bortolato and colleagues introduced the concept of cognitive remission as an additional aim in the treatment of affective disorders [10]. Importantly, cognitive side-effects after ECT are perceived by patients as the most disturbing due to their negative impact on quality of life [11] and a descriptive systematic review by Rose and colleagues showed subjective memory loss in 29 to 55% of patients 6 months after ECT [12]. In fact, the reluctance patients express to undergo a treatment with ECT is partially based on the expected cognitive side effects.

In an extensive meta-analysis that included 84 within-subjects designed studies (a total number of almost 3000 subjects and 24 different cognitive variables) using optimal stimulation parameters, Semkovska & McLoughlin found a short-term decrease in a broad range of cognitive control processes [13]. Cognitive control refers to processes that allow information processing and behavior to vary adaptively and flexibly depending on current goals [14], and includes a broad class of mental operations such as (working) memory, attention, and concentration. These cognitive deficits remain within 3 days following ECT treatment, followed by recovery in the two subsequent weeks except from deficits in episodic retrograde (i.e., autobiographical) memory. Most importantly, these cognitive side effects of ECT, even though transient, might trigger mechanisms that increase relapse in depressed patients. Indeed, based on the available cross-sectional, prospective and longitudinal research, reduced cognitive control is an important neurobiologically driven vulnerability factor for depression (for a review, see De Raedt & Koster, 2010) [15]. Intensive research has shown that deficient cognitive control is a crucial vulnerability factor for recurrent depressive episodes. Moreover, repetitive negative thinking (RNT) is a key vulnerability mechanism in depression and research suggests that the inability to interrupt RNT is linked to inadequate cognitive control [16–19].

Recently, researchers have started to investigate computerized cognitive control training to improve depression and cognitive risk factors with encouraging results. Cognitive Control Training (CCT) uses a basic cognitive task that strongly loads on working memory and cognitive control processes, namely the adaptive Paced Auditory Serial Addition Task (aPASAT). During this task individuals are presented with a digit every 3 s and are asked to add every two consecutive digits. Task difficulty is modified based on the individuals’ current task performance, allowing training of cognitive control. This task is well-validated as a tool to remediate depression-related cognitive impairments. Moreover, the training puts low emphasis on the visual and auditory abilities of patients. Siegle et al. (2007) combined treatment as usual with several sessions of cognitive control training over a two-week period in depressed patients [20]. This approach resulted in reduced rumination and depressive symptomatology compared to a treatment as usual control group. In a later research report, Siegle et al. (2014) provided first evidence for long-term benefits of cognitive control training, showing reduced need for clinical care during a one-year follow-up period [21]. Meanwhile, other researchers have replicated beneficial effects of cognitive control training on depressive symptomatology in clinical samples [22, 23]. Positive effects were also found on stress reactivity and maladaptive emotion regulation in vulnerable people 1 month after the intervention [24]. A recent RCT in remitted depressed patients using the same training tool as we propose in the current project, showed reduced cognitive vulnerability, less residual depressive symptoms, reduced constraints in daily life and even increased resilience (measured 3 months after the intervention) [25]. Indeed, a recent systematic review (including 34 experimental studies) demonstrated that cognitive control training could be used as an add-on preventive and/or curative intervention in the treatment of depression [25]. Therefore, this cognitive remediation intervention seems to be an important non-pharmacological intervention for relapse prevention and could be promising in patients that partially or fully responded to ECT.

Provided that early studies suggest that task engagement is important for beneficial effects of CCT and facial features are an indicator of learning and engagement [26], depressive symptomatology [27, 28] and cognitive functioning [29], the current research will use facial video footage to record physiological responses during CCT. Monitoring facial expressions via videotape is a non-intrusive manner to further explore the mechanisms underlying effects of CCT. Over the years, many researchers have attempted to identify facial expressions indicative of depressive symptomology [28, 30] as well as frustration and engagement [26]. Whereas the labelling of patients’ facial expression used to be lengthy and costly operations, recent developments in technology enable us to use automated classification algorithms to gain insight in patients’ videotaped facial expressions [31]. Due to the disease burden of this specific patient group, collecting data in a passive and non-intrusive fashion (no extra constraints on patients’ workload) could bring forth novel insights in the effects of CCT and depression. In order to explore mechanism of action of this cognitive control training, exploratory analysis will be conducted with regards to video footage collected during the CCT and the active placebo phase of the study.

## Methods

### Aims

A first aim of this randomized-controlled trial is to assess the effects of cognitive control training (CCT) compared to an active placebo condition following (partial) clinical response (at least a 25% reduction of clinical symptoms) to ECT on depression symptomatology, cognition, cognitive complaints and quality of life. Secondly, given that the application of ECT is reserved for the most severely ill patient population characterized by high chronicity and that cognitive side effects due to ECT might be mechanisms that increase risk of relapse, cognitive remediation interventions targeting cognitive control mechanisms could be a promising relapse prevention strategy in patients that partially or fully responded to ECT. As such, given that the risk of relapse is greatest within the first 6 months following ECT [8], we will monitor patients every 2 weeks within that timeframe, allowing detection of potential relapse of depression. Thirdly, we will assess patient evaluation of the addition of cognitive control training to ECT using qualitative interview methods. Finally, in order to further advance our understanding of the mechanisms underlying effects of CCT, exploratory analyses will be conducted using video footage collected during the CCT/active control phase of the study.

### Hypotheses

On our primary outcome measure, depressive symptomatology as measured by HAM-D, BDI-II and RDQ, we expect a reduction in patients that received 2 weeks of CCT as compared to the active placebo condition following ECT. On our secondary outcome measures we expect [1] reduced cognitive complaints (SSMQ), [2] improved cognitive functioning (CANTAB, PASAT), [3] reduced rumination (RRS-10, 4) enhanced quality of life (QLDS) in patients that received the cognitive control training compared to active placebo. These effects are expected immediately after the CCT as well as within the 6 months follow up period. Beneficial effects will also be reflected in reduced risk for relapse of depression during the period of 6 months follow-up. Moreover, we expect more positive treatment evaluations by both patients and their peers, increased patient satisfaction and acceptability of ECT in patients that received CCT as compared to an active placebo condition following clinical response ECT.

### Study design and setting

This study uses a single blind mixed methods randomized controlled superiority trial with an embedded qualitative component. Participants will be recruited from one study site in a rural ECT-clinic in Belgium. Eligible participants will be encouraged to participate through flyers and posters in the ECT-clinic. Referring physicians will be informed of the study protocol. Participants will give informed consent for the study, cognitive control training or placebo post-ECT, prior to the start of electroconvulsive treatment.

The study has one intervention arm (cognitive control training) and one active placebo arm. All patients who give consent for participation and who fulfil the inclusion criteria will be randomized. Upon registration in the computer-based training by the allocated researcher, the computer will randomly allocate participants to either cognitive control training or placebo condition (e.a., computerized full random number generator). The researcher will monitor adherence to placebo or cognitive control training. Outcome assessors or ECT-physicians will only be involved in recruitment, ECT and post-intervention follow-up. They will not be involved during the two-week intervention phase of the study. Thus, randomization will be conducted without any influence of the principal investigators or outcome raters and both outcome assessors, ECT-physicians and participants will be blinded. Study data will be collected using digital and paper forms. Only outcome assessors and researchers will have access to the data. Data will be stored on a secure, password-controlled, server hosted at Ghent University. Qualitative interviews will be conducted in both arms after completion of CCT or placebo training. This study is in accordance with the Declaration of Helsinki (2013) and approved by the Ethical Committee of the Ghent University Hospital.

### Inclusion and exclusion criteria

Patients will be asked to participate in the current study as soon as they consent to ECT and before ECT is started. Depression diagnosis will be confirmed based on the Diagnostic and Statistical Manual (DSM-5) diagnostic criteria for major depressive episode using the screening items and depressive episode module (A) of the semi-structured Mini International Neuropsychiatric Interview (MINI v7.0.0). Both patients suffering from unipolar depression and bipolar depression are eligible. Treatment resistance, defined as non-response to two treatment trials with drugs from a different pharmacological class, each used in an adequate dose for an adequate time period in the current episode [32, 33], will be checked by the investigator (a certified psychiatrist) at inclusion. Severity of depressive symptoms will be measured by the BDI-II and the HAM-D. Patients with neurological and/or neurodegenerative disorders will be excluded using the Montreal Cognitive Assessment (MOCA< 18) at the beginning of the ECT course.

Inclusion criteria are (a) current major depressive episode with treatment resistance, (b) eligibility and consent for ECT treatment, (c) ability to consent to the study, (d) aged between 18 and 70 years old. Exclusion criteria are (a) neurodegenerative disorder or MOCA < 18, (b) catatonia, (c) schizophrenia, (d) alcohol use disorder in the previous year, (e) prior treatment with ECT, (f) insufficient computer knowledge or analphabetism.

### ECT protocol

Patients will receive ECT treatment with a MECTA SpECTrum 5000Q device based on the current standards [34, 35]: ultra-brief pulse (0.3 pulse width) with a right unilateral stimulus (RUL), a dose titrated relative to the patient’s own seizure threshold and an optimized anesthesia technique. BDI-II will be administered weekly to monitor clinical progress. If patients fail to respond after 6 RUL ECT sessions, switch to bitemporal electrode position will be considered. If there is no clinical response, ECT will be stopped after 12 sessions. If there is clinical response, ECT will be stopped when clinical remission is achieved or if there is no more clinical improvement after two subsequent sessions.

### Procedure

Outcome assessors and/or ECT-physicians will provide adequate verbal and written information regarding the study to all eligible patients at the ECT-clinic. Researchers will obtain written informed consent from all patients willing to participate and able to give consent. After consenting to participate and before the start of ECT treatment, all patients will complete baseline cognitive function assessment (CANTAB, PASAT), cognitive complaints (SSMQ), depressive symptomatology (BDI-II, HAM-D), depressive status (RDQ), rumination (RRS-10) and quality of life (QLDS). After ECT completion, cognitive functioning (CANTAB, PASAT), cognitive complaints (SSMQ), depressive symptomatology (BDI-II, HAM-D), depressive status (RDQ), rumination (RRS-10) and quality of life (QLDS) will be assessed. Moreover, all patients will receive standard clinical care. Patients will receive standard pharmacological relapse prevention, under the responsibility of their treating physician, started during (nortriptyline) or after (lithium) ECT by combining nortriptyline (50-150 ng/ml) and lithium (≥0.5 mmol/l) for MDD and lithium (≥ 0.5 mmol/l) alone for BDD. In case of contra-indication for nortriptyline and/or lithium, alternative relapse prevention options will be explored by the treating physician. As is standard clinical care, monthly lithium dosing and testing of renal and thyroid function will be performed by the treating physician. If renal function deteriorates during follow-up this should be reported as an adverse event and may necessitate lithium discontinuation. Before dismissal from the ward participants will receive a two-session CBT-based relapse prevention group therapy and individual counseling by a social worker. Only patients who achieve a 25% or more reduction in BDI-II or HAM-D scores [36] will be randomly assigned to one of two conditions (CCT or active control), see Fig. 1 as cognitive control training has evidence as a relapse prevention strategy and not as a treatment for MDE. Non-responders to ECT will be excluded to allow further clinical treatment for MDE outside of this study protocol. After completion of the CCT, relapse of depression will be monitored for a period of 6 months using mobile assessments of depression (every 2 weeks) and telephone interviews in case of possible relapse. If there is an indication of relapse, patients will be assessed by the semi-structured Mini International Neuropsychiatric Interview (MINI v7.0.0) depressive episode module (A) and referred for psychiatric assessment to their treating psychiatrist for adequate clinical care if necessary. Patients who relapse will be excluded only if they receive a subsequent ECT-course as this might affect cognitive parameters. At three and 6 months, a more extensive evaluation will be performed investigating cognitive parameters (SSMQ), depressive symptomatology (BDI-II, HAM-D), depressive status (RDQ), rumination (RRS10) and quality of life (QLDS). We refer to Fig. 2 for an overview of the study design and Table 1 for the trial registration data set.

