Primary outcome(s)	Change in severity of depressive symptoms, clinician-rated (HAM-D) Change in severity of depressive symptoms, self-reported (BDI-II) Change in depressive symptoms and quality of life, self-reported (RDQ) Time Frame:1–7 days before first ECT session, 1–7 days post ECT completion, 1–7 days after intervention/placebo completion, 3 months after ECT completion, and 6 months after ECT completion
Key secondary outcomes	Subjective memory complaints (SSMQ) Time Frame:1–7 days before first ECT session, 1–7 days post ECT completion, 1–7 days after intervention/placebo completion, 3 months after ECT completion, and 6 months after ECT completion Quality of Life in Depression Scale (QLDS) Time Frame:1–7 days before first ECT session, 1–7 days post ECT completion, 1–7 days after intervention/placebo completion, 3 months after ECT completion, and 6 months after ECT completion Rumination (RRS-10) Time Frame:1–7 days before first ECT session, 1–7 days post ECT completion, 1–7 days after intervention/placebo completion, 3 months after ECT completion, and 6 months after ECT completion Cognition (CANTAB) Time Frame:1–7 days before first ECT session, 1–7 days post ECT completion, 1–7 days after intervention/placebo completion, 3 months after ECT completion, and 6 months after ECT completion Cognition (Paced Auditory Serial Addition Task - PASAT) Time Frame:1–7 days before first ECT session, 1–7 days post ECT completion, 1–7 days after intervention/placebo completion, 3 months after ECT completion and 6 months after ECT completion Acceptability and satisfaction: Qualitative interviews Time Frame: 1–30 days after CCT training completion Time to relapse Time Frame:Up to 6 months monitoring Facial features from video footage Time Frame:2 weeks during CCT or placebo intervention

**Table 2 Tab2:** Summary of protocol amendments

Protocol version	
1. December 2017	Original
2. August 2018	Qualitative interviews added
3. December 2019	Overall changes to protocol - Changes in outcome parameters (SSMQ, RDQ) - Changes to aPASAT training - Inclusion of facial videotaping - Extension of study duration

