#### Assessment of depression relapse

Patients will receive a text message once every 2 weeks (except at 3 and 6 months post-ECT; when they are invited for a more thorough interview at the hospital) to enquire whether they experienced either core symptom of depression over the past 2 weeks: 1) Have you been consistently depressed or down, most of the day, nearly every day, for the past 2 weeks?; 2) In the past 2 weeks, have you been much less interested in most things or much less able to enjoy the things you used to enjoy most of the time? . Answer can be yes or no. The text messages will be sent using SurveySignal at 18.00 h containing a link to a two question LimeSurvey questionnaire. If the patient does not respond within the first hour, a reminder text message will be sent. If the patient either does not respond to the screening questions within a 24-h timeframe, or answers either of the questions affirmatively, the patient will be called by the researcher to conduct the semi-structured Mini International Neuropsychiatric Interview (MINI v7.0.0) depressive episode module (A). If a relapse has concluded, patients will be referred for psychiatric assessment to their treating psychiatrist for adequate clinical care. These phone calls will be recorded and stored for later evaluative purposes and diagnosis by an independent rater.

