### Data management and analyses

Participant files, including informed consent forms, will be stored in a locked cabinet with restricted access for a period of 20 years after study completion.

We will use a 4 (time: T2, T3, T4, T5) by 2 (condition: active placebo CCT; real CTT) repeated measures design. The significance level will be set at α = .05.

For our main analyses, we will rely on intention-to-treat analysis (ITT) to model effects of CCT on the outcome measures of interest, using the Last-Observation-Carried-Forward (LOCF) method to handle missing data (due to non-response, drop-out or relapse of depression). Where adequate, effects of CCT on our cognitive measures and questionnaire data will be modeled using repeated measures Analysis of Variance (ANOVA) or Covariance (ANCOVA). Significant interaction effects will be further explored using independent and paired samples *t*-tests. Effects of CCT on relapse of depression will be modeled using a Pearson Chi-Square test. In addition, we will conduct survival analyses (Kaplan Meier estimator) to model time to relapse, using the log-rank test to compare the obtained survival curves.

Qualitative data analyses methods will be used to analyze the interviews regarding satisfaction, acceptability, and appropriateness of the design.

Exploratory analyses will be used to investigate the facial video footage data collected during the ten sessions of CCT or active placebo. From the footage, we will deduce facial landmarks and reactions during the performance of the training as an indication of frustration, engagement and general mood, whereas different factors could be of influence on the effectivity of the training. More specifically, we expect to see differences in, e.g., general facial valence, facial muscle tension and frustration.

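### Relapse monitoring is dated from the end of training but justified and visit-scheduled from the end of ECT, so 6-month relapse has no single window and time zero falls about 2 weeks after randomisation

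*Protocol article*

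**What the plan says.** Two sections start relapse monitoring when training ends. Procedure: "After completion of the CCT, relapse of depression will be monitored for a period of 6 months". Abstract, Method/design: "we will monitor patients every 2 weeks for a period of 6 months following CCT/active placebo".

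Aims gives the reason for the window as "given that the risk of relapse is greatest within the first 6 months following ECT" and places the fortnightly monitoring inside that same period.

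The two hospital visits within the monitoring period are dated from ECT. Assessment of depression relapse describes a text every 2 weeks, "except at 3 and 6 months post-ECT; when they are invited for a more thorough interview at the hospital". Table 1 dates the depression scales "1–7 days after intervention/placebo completion, 3 months after ECT completion, and 6 months after ECT completion". The relapse entry in that table reads only "Time to relapse Time Frame:Up to 6 months monitoring".

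Study design and setting has the computer allocate patients on registration in the training program. Intervention group and Control group allow up to 7 days between ECT and the start of training. Participant retention and withdrawal allows 14 days for the 10 sessions.

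On analysis, Data management and analyses says "Effects of CCT on relapse of depression will be modeled using a Pearson Chi-Square test". It then adds Kaplan-Meier curves with a log-rank test for time to relapse.

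**The concern.** A relapse endpoint needs one origin, one end and the same ascertainment throughout. Here an analyst could take 6 months from the end of training or 6 months from the end of ECT and cite the protocol for either. A relapse that falls between the two ends counts under one reading and not under the other.

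The origin matters as well. Patients are randomised before training, but the described relapse checks begin after it. In between, no text screen and no MINI is described. A patient who stops training early has no completion date to start the clock, and Intervention group says that patients who miss too many sessions are excluded. That sits badly with the intention-to-treat principle stated for the main analyses.

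A smaller gap lies at the visits. The text is skipped at 3 and 6 months, and the visit battery listed in Procedure does not include the MINI, which is the instrument used elsewhere to establish a relapse.

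**Working it through.** **The plan's own figure.** N for the chi-square: (1.960 + 0.842)² / 0.3² = 7.85 / 0.09 = 87.2, rounded up to 88; power at 88 is 0.80. The stated N reproduces, and nothing below changes it.

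**The dates side by side.**

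| Place | What is dated | Clock |
|---|---|---|
| Abstract; Procedure | relapse monitoring, 6 months | end of training |
| Aims | relapse monitoring, reason for the window | end of ECT |
| Table 1; RDQ; Assessment of depression relapse | 3- and 6-month visits | end of ECT |
| Table 1, time to relapse | up to 6 months | not stated |

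**Distance between the clocks.** From end of ECT to end of training is at most 7 + 14 = 21 days. From randomisation to end of training it is about 14 days, because allocation takes place on registration in the training.

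**Inputs for size.** 6-month relapse 37.7% (Background) or 50% (Abstract); odds ratio 0.38 (Sample size calculation). Assumptions: 44 per arm (the ratio is not stated), constant hazard, 6 months = 182.6 days.

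**Effect on the 6-month proportion.** Cumulative risk at day 182.6 + d is 1 − (1 − p)^((182.6 + d)/182.6).
- p = 37.7%: 39.9% at d = 14 and 41.0% at d = 21.
- p = 50%: 52.6% and 53.8%.

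**Events between randomisation and the end of training.** At a 37.7% control rate:
- CCT odds: 0.38 × 0.377/0.623 = 0.230, so CCT risk = 0.230/1.230 = 18.7%.
- Total expected: 44 × 0.377 + 44 × 0.187 = 24.8.
- Risk in 14 days, 1 − (1 − p)^(14/182.6): control 3.56%, CCT 1.57%.
- Expected in 14 days: 44 × (0.0356 + 0.0157) = 2.3, about 9% of 24.8.
- Over 21 days, counted from ECT: 44 × (0.0530 + 0.0235) = 3.4. This includes time that may precede randomisation.

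At a 50% control rate the CCT risk is 27.5% and the total is 44 × (0.500 + 0.275) = 34.1. The 14-day count is 44 × (0.0518 + 0.0244) = 3.4, about 10%. A hazard concentrated soon after ECT would raise these shares.

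**Chi-square against log-rank.** Simulation with 44 per arm, odds ratio 0.38, 4000 runs, and drop-outs without a prior relapse counted as no relapse. With 5-10% equal loss, power is 0.50-0.52 for both tests at a 37.7% control rate. At 50% it is 0.57-0.59 (chi-square) and 0.58-0.59 (log-rank). Type I error is 0.04-0.06 for both. These powers are below 0.80 because the odds ratio, not w = 0.3, was simulated; that is a separate matter.

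**The case against.** **The dates need not conflict.** Table 1 and the relapse section date visits and scales from ECT, not the monitoring period. Texts counted from training and visits counted from ECT can coexist. Only Aims ties the monitoring itself to ECT, and the study-flow figure, not available here, may show the clock. The first part is correct: the visit dates alone are no contradiction. What stands is that Aims and Procedure give different windows, the visits take the place of texts within one schedule, and the time-to-relapse entry names no origin.

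**Early relapses are not simply lost.** A reader might infer that they are. But HAM-D, BDI-II and RDQ are taken 1-7 days after training, each text looks back 2 weeks, and a yes or a non-response leads to a MINI call. An episode that begins during a 14-day training period would mostly surface soon afterwards. So misdating is the main effect, and a missed relapse is plausible chiefly in patients who stop training.

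**The randomised comparison is not shown to be broken.** Intention-to-treat is stated, follow-up of every randomised patient is promised, and the gap is the same in both arms.

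**The chi-square is not the only relapse test.** A reader might infer that censoring is ignored. The protocol plans Kaplan-Meier and log-rank in the next sentence, and the simulation shows almost no power difference at the expected loss if it is balanced. Dropping the chi-square would be a preference, and it would detach N from the test that set it.

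**The visits may capture relapse.** BDI-II and HAM-D are given at 3 and 6 months, the BDI-II is meant to monitor possible relapse, and Procedure calls for the MINI on any indication of relapse. The fuller interview could include it. The text does not say that it does, nor which finding would trigger it. If monitoring runs from training, it also continues past the 6-month post-ECT visit, so the window ending at that visit is the last one only on the ECT clock.

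**Conclusion.** The point holds as one of definition and ascertainment. The protocol supports two 6-month relapse windows whose ends differ by up to about 3 weeks. That moves cumulative relapse by about 2-3 percentage points at a 37.7% rate and about 3-4 at 50%. The stated start of monitoring is about 2 weeks after randomisation, and about 2-3 of about 25 expected relapses fall in that interval without a described text or MINI check. With so few events, reassigning two or three can matter to the result.

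The sizes rest on a constant hazard, 44 per arm and the cited odds ratio applying throughout. Bias, as distinct from imprecision and misdating, requires early relapse or non-completion to differ between arms. The document gives no evidence either way. The 3-week figure measures the difference between the clocks and should not be read as the unmonitored time after randomisation.

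**What to change.** 1. Define relapse and time to relapse from randomisation, for all randomised patients whether or not they finish training, to one stated end. A fixed time from randomisation gives every patient the same window. If the 6-month post-ECT visit is preferred as the end, say so, and note that follow-up will then vary by up to about 7 days.
2. Ask the two existing screening questions at the post-training, 3-month and 6-month visits, with MINI module A if either is positive. At the post-training visit, word the look-back to reach randomisation.
3. Align the abstract, Aims, Procedure, Table 1 and Assessment of depression relapse on that origin and end.
4. Use the already planned Kaplan-Meier and log-rank analysis to handle drop-outs by censoring. Keep the chi-square as the test on which N was based.

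The cost is wording plus two yes/no questions at visits already held, with an occasional MINI module. Sample size is unaffected.
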